#### Secondary outcomes

The secondary outcomes are:Cardiac health outcomes:Resting blood pressureResting HRResting HRVRecovery HRPhysical functionCardiorespiratory fitnessUpper limb strengthLower limb functionalitySelf-reported physical activity levelHealth-related quality of lifeFatigue

### Assessment of the primary outcomes

#### Resting LV ejection fraction and resting LV longitudinal strain

Resting LV ejection fraction will be calculated using the biplane method of disks (modified Simpson’s rule) from the apical four-chamber and two-chamber view [30]. For resting LV global longitudinal strain assessment, two-dimensional grayscale images will be acquired in the apical four-chamber, two-chamber, and three-chamber views, with a frame rate of 60–100 frames per s (fps). Three cardiac cycles will be digitally stored and Velocity Vector Imaging (VVI) software (Siemens Medical Solutions United States of America Inc) will be used in the analysis. Echocardiographic acquisitions will be performed by a single experienced cardiologist blinded to the patient assignment group.

#### Circulating NT-proBNP levels

Non-fasting venous blood samples will be drawn by a nurse oncologist. The assessment of NT-proBNP levels will be conducted in the local clinical analysis laboratories at the CHVNG/E, which are certified by the UK National External Quality Assessment Service. These professional staff will be blinded to the patient assignment group.

### Assessment of the secondary outcomes

#### Resting blood pressure and resting HR

Resting blood pressure (systolic and diastolic blood pressure) and resting HR will be measured using a standard automated device (Philips SureSignsVM6 (Philips Medical System, Andover, USA)). Two measurements will be carried out. The first measurement will be preceded by a 5-min resting period and a second reading will be taken after 3 min. If necessary, additional records shall be obtained until two consecutive stable measurements (differences < 5 mmHg for blood pressure and < 7 bpm for HR) are obtained. The average of the two stable measurements will be used in the analysis. This procedure will be carried out by a study investigator (ALA) not blinded to the patient assignment group.

#### Resting HRV

HRV is a non-invasive method used to analyze cardiac autonomic function through the measurement of successive heartbeat variations (R-R). Resting HRV will be analyzed using a HR monitor Polar V800 (Polar Electro Oy, Kempele, Finland) with a Polar H7 chest strap. During the R-R recording, patients will be seated in a comfortable position. They shall be required to breathe spontaneously, to avoid any movements, and to maintain neutral thoughts during the data acquisition. The first 5 min will be excluded (stabilization period) and the remaining 5 min will be used to calculate the time-domain (standard deviation of successive normal R-R (SDNN), and root mean square of successive normal R-R (RMSSD)) and frequency-domain indices (low-frequency spectral component (LF), and high-frequency spectral component (HF)). In all cases, the R-R recordings will be exported to the Kubios v2 HRV software (Biosignal Analysis and Medical Imaging Group at the Department of Applied Physics, University of Kuopio, Kuopio, Finland). Occasional artifact noise shall be automatically replaced with the interpolated adjacent RR interval values (filter power < low). This procedure will be carried out by the first author (PA) who will not be blinded to the patient assignment group.

#### Recovery HR

Recovery HR will be determined as the absolute difference between the HR at peak effort during the cardiorespiratory exercise test (CRET) and the HR at 60 s, and 120 s post-exercise. HR values will be derived from a continuous record obtained via CRET (Mortara X-Scribe, Mortara, USA). This procedure will be carried out by study investigators (EV, MT), blinded to the patient assignment group.

#### Cardiorespiratory fitness

Cardiorespiratory fitness will be evaluated by means of a symptom-limited CRET on a treadmill (Mortara X-Scribe, Mortara, USA), using a modified version of the Bruce protocol [31]. Expired gases will be continuously collected throughout exercise and analyzed for ventilatory volume (VE) and for oxygen (O2) and carbon dioxide (CO2) content, using dedicated analyzers. Standard spirometry (forced expiratory volume in 1 s (FEV1)) and forced vital capacity (FVC) will also be undertaken before the test. Equipment calibration and measurements will be in accordance with the recommendations of the American Thoracic Society and American College of Chest Physicians [32]. The following parameters will be calculated and considered for analysis: peak oxygen consumption (peak V̇o_2_, measured in milliliters per kilogram per minute), peak respiratory exchange ratio (RER), defined by the ratio of CO2 production to O2 consumption at peak effort, oxygen consumption at the anaerobic threshold (AT), defined as the point at which CO2 production increases disproportionately in relation to O2 consumption, obtained from a graph plotting O2 consumption against CO2 production, and total exercise duration (measured in seconds). The maximum HR achieved will also be recorded. The CRET will be conducted on a separate day to the remaining outcomes assessments out by study investigators (EV, MT) blinded to the patient assignment group. Patients will be in a fasted state and will not be asked to discontinue current medication before the test.

#### Upper limb strength

Upper limb strength will be evaluated by maximal voluntary grip strength (measured in kilograms), using a digital handgrip dynamometer (Saehan Corporation, Masan, South Korea - model SH5003). Each subject will perform six trials, three in each arm, with an alternating bilateral sequence. The results will based on the average of the three trials, respectively. This procedure will be carried out by the first author (PA), not blinded to the patient assignment group.

#### Lower limb functionality

Lower limb functionality will be evaluated by the sit-to-stand test using a straight-backed chair (40 cm high). Each subject will be required to keep plantar support while flat on the floor with arms crossed at the chest, and sit and stand as many times as possible for 30 s. The score for the test will be determined by the number of repetitions achieved during this procedure. The procedure will be carried out by the first author (PA), not blinded to the patient assignment group.

### Self-reported physical activity level

The International Physical Activity Questionnaire-Short (IPAQ-SF) will be used to calculate the metabolic equivalent (MET) minutes per week spent in walking and in moderate and vigorous activities. Sedentary behavior will be determined based on time spent sitting per day (minutes). Based on their scores, participants will be categorized as having a low, moderate, or high physical-activity level. The Portuguese language version of the IPAQ-SF will be used [33]. Scoring will be analyzed by the first author (PA), not blinded to the patient assignment group.

#### Health-related quality of life and fatigue

The European Organization for Research and Treatment in Cancer (EORTC) Quality of Life C-30 (QOL-C30) is a self-administered, validated questionnaire to assess HR-QOL in patients with cancer [34]. It is composed of nine multi-item scales: five functional scales (physical, role, cognitive, emotional, and social), three symptom scales (fatigue, pain, and nausea and vomiting), and a global health and quality-of-life scale. Additionally, there are five single items of symptoms commonly reported by patients with cancer (dyspnea, sleep disturbance, appetite loss, constipation, and diarrhea), and an item that evaluates the perceived financial impact of the disease. In this study, the third version of this questionnaire will be used, in the Portuguese language [35]. Analyses will include the five functional scales, fatigue scale, and the global health and quality-of-life scale. The scoring of the several scales will be carried out by the first author (PA), not blinded to the patient assignment group.

### Demographic, anthropometric, and clinical data

Demographic, anthropometric, and clinical data will be recorded during the enrolment process (**−**t_0_). Demographic data include age, sex, and education. Anthropometric data include weight, height, and body mass index. Clinical data include disease, treatment information, past medical history, and current medication. These data will be extracted from the patients’ electronic medical files by two study coordinators (ALA, AJ) not blinded to the patient assignment group.

### Safety

The safety of the intervention will be assessed by weekly tracking and monitoring the number of adverse events according to the National Cancer Institute Common Terminology Criteria for Adverse Events version 4.0 (https://ctep.cancer.gov/protocoldevelopment/electronic_applications/ctc.htm). A meeting between the study investigators will be held weekly to review and discuss the reported adverse events. All serious adverse events will be immediately reported to the CHVNG/E ethics commission and to all study members, and will be reported in the study results. Adverse events will be evaluated by the study investigators who will make the decision to stop the study early if there is a clinically relevant increased risk.

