### Blinding

This study will involve the prescription of exercise sessions. To carry out a rigorous exercise prescription and to ensure adequate follow up of each patient, participants, the physical trainer (PA), the medical oncologist (AJ), and the nurse oncologist (ALA) will not be blinded to group assignment. Due to the lack of resources, only the evaluators acquiring the echocardiographic outcomes (resting LVEF and LV global longitudinal strain), circulating NT-proBNP levels, cardiorespiratory fitness, and recovery HR data, will be blinded to the group assignment.

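### The safety rules put blinded assessors on the adverse-event review path with no stated safeguard, so assessor blinding is at avoidable risk

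*Protocol article*

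**What the plan says.** Two sets of rules bear on this point.

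**Blinding.** The Blinding section says that participants, the trainer, the medical oncologist and the nurse oncologist know the allocation. For lack of resources, blinding is confined to "only the evaluators acquiring the echocardiographic outcomes (resting LVEF and LV global longitudinal strain), circulating NT-proBNP levels, cardiorespiratory fitness, and recovery HR data". The assessment sections give the roles:
- Echocardiographic acquisition is "performed by a single experienced cardiologist blinded to the patient assignment group".
- NT-proBNP is measured by blinded laboratory staff.
- For recovery heart rate the text reads "This procedure will be carried out by study investigators", and describes them as blinded. The Cardiorespiratory fitness section gives the exercise test to the same two people, again as blinded study investigators.

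**Safety.** The Safety section sets the purpose: "The safety of the intervention will be assessed by weekly tracking and monitoring the number of adverse events". It then states "A meeting between the study investigators will be held weekly to review and discuss the reported adverse events". Serious events have a wider audience: "All serious adverse events will be immediately reported to the CHVNG/E ethics commission and to all study members". The study investigators also evaluate the events and are the ones "who will make the decision to stop the study early if there is a clinically relevant increased risk". The Sample size calculation section repeats that last provision.

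**The concern.** The safety rules name their audience by broad terms, and those terms take in people whom the blinding rules are meant to shield. The trainer, oncologist and nurse who would bring the events to the table know every patient's allocation. The blinded assessors then test the same patients at t2 and t3, after those discussions.

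Patients and treating staff are open, so assessor blinding is the main protection against detection bias. The exercise test is symptom-limited, so an assessor's conduct could influence when a patient stops, and with it peak oxygen consumption and the heart-rate recovery that follows. If the echocardiographer were also reached, two of the three primary outcomes would rest on images acquired by one operator who might know the arm. Any leak would also be uneven: it would occur mainly for exercise-arm patients who had events. The Limitations section mentions the open design only for its effect on retention in the control group.

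**Working it through.** The point depends on no numerical figure in the plan, so the check is a comparison of sections.

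**1. Whom does the weekly meeting include?** The Safety section says study investigators, without limiting the role. Elsewhere the article uses that term for unblinded people (the blood-pressure assessor; the two data managers, who are the trainer and the oncologist) and for blinded people (the two exercise-test assessors). The term does not separate the two groups, and no other sentence does.

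**2. Whom do serious-event notices reach?** All study members, a phrase the article does not define.

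| Blinded assessor | Outcome | Called a study investigator? | Exposed to |
|---|---|---|---|
| Two exercise-test assessors | Cardiorespiratory fitness, recovery heart rate (secondary) | Yes | Weekly meeting, event evaluation, serious-event notices |
| One cardiologist | LVEF, strain (primary) | No | Serious-event notices, if counted as a study member |
| Laboratory staff | NT-proBNP (primary) | No | Serious-event notices, if counted as study members; an assay leaves little room for assessor influence |

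**3. Could the arm come out without anyone stating it?** Yes, for some events. The Resistance training section ties adverse events to particular exercises when deciding whether to add load. The Usual care group section offers controls the program only after their final assessments. Until then, an event linked to a supervised session can arise only in the intervention arm, so describing it reveals the allocation. Judging whether the intervention raises risk would also ordinarily need a comparison by arm.

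**4. Is there a safeguard elsewhere?** The Data management section codes patients, but that protects identity, not arm, and the authors involved in the trial can see full identities. No section says that meetings or notices mask the allocation. None says that they disclose it.

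**5. Timing.** The program starts 1–2 days after the first chemotherapy session and runs through treatment. t2 falls 1–5 days after chemotherapy ends and t3 three months after t2. Both follow the period in which session-linked events would be discussed.

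**6. Can it be sized?** From 1 November 2018 to 30 June 2021 is 972 days, and 972 / 7 = 138.9, so at most about 138 weekly meetings. That is a ceiling on opportunities, not a count of unblindings. Neither the number of session-linked events nor the effect of knowing the arm on a measurement is given.

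**The case against.** The strongest reply is that no contradiction exists. One section says that certain evaluators do not know the arm; another says that events are discussed and reported. Both hold if reports omit the allocation. Both arms receive anthracycline chemotherapy, so most adverse events would not identify the arm. **This stands.** A reader might infer that the plan breaks its own blinding, or that the two sets of rules cannot both be followed. The document does not support that, because nowhere does it say that the arm is revealed.

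A second reply is that attendance lists and masking of event reports are operational detail which an article leaves to the full protocol. This carries some weight, but the article is not silent. It states who meets and who is notified, in terms that include blinded staff. The point is about that stated rule.

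A third reply is that the link to the primary outcomes is thin. **This also stands.** The only documented overlap is with secondary outcomes. The cardiologist is never called a study investigator and is reached, if at all, only by serious-event notices.

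A reader might also be tempted to size the bias on LVEF. Take an assumed SD of 5 points and an assumed operator shift of 1 to 2 points; neither is in the document. If every patient in one arm were affected, the shift would be 1/5 = 0.2 to 2/5 = 0.4 SD, or 0.2/0.6 = 33% to 0.4/0.6 = 67% of the planned effect size of 0.6. If only 10% of that arm were affected (again assumed), the arm mean would move by 0.1 to 0.2 points, or 0.02 to 0.04 SD, about 3% to 7% of 0.6. A range of 3% to 67% driven wholly by assumptions is not an estimate, and the point does not rest on it.

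**Conclusion.** The concern holds as a risk to blinding. On a literal reading, two blinded assessors of secondary outcomes belong to the group that reviews adverse events of the exercise program each week alongside unblinded colleagues. Some of those events would identify the arm. For LVEF and strain the exposure is conditional: it needs the undefined group of study members to include the echocardiographer, and it covers serious events only. For NT-proBNP it is negligible in practice.

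This rests on two readings: that study investigators means the same in the Safety section as in the exercise-test sections, and that session-linked events would be described as such. Actual unblinding is not shown, and the bias cannot be quantified from the document. The point is a cheap improvement to a stated rule, not a flaw that undermines the trial.

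**What to change.** - In the Safety section, and in the matching sentence of the Sample size calculation section, limit the weekly meeting, the evaluation of events and the serious-event notices to the unblinded investigators and the ethics commission. Changing the meeting alone would leave the blinded assessors among those who evaluate events.
- Where a blinded assessor needs a clinical fact before a test, pass it on without the arm and without reference to exercise sessions.
- Record any accidental unblinding of an echocardiography or exercise-test assessor, so that it can be reported with the results.

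The cost is a few sentences in two sections and a shorter distribution list, with no added staff or assessments. The small downside is that the blinded assessors no longer take part in routine adverse-event review. The change concerns only who takes part and who is told; it leaves the clinical criteria for acting on events as they are.

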### Data management

Study data will be managed by two study investigators (PA, AJ) using a predesigned data collection form (Microsoft Office Excel version 2016 (Microsoft Corporation, Redmond, WA, USA) and Statistical Package for the Social Sciences files version 23.0 (IBM Corporation, Armonk, NY, USA)) with double data-entry. Data checks will be regularly performed to ensure data quality. Patients will be identified by codes to ensure their anonymity, and only the authors involved in the trial will have access to their full identification details. The total number of patients who meet the study eligibility criteria will be recorded, as will the number of patients who agree or not agree to participate in the study, the number of patients assigned to each study arm, the number of patients who participate in all sessions, the attendance of each patient in the intervention sessions, the number of patients who provide follow-up data, the number of patients included in the final analysis, and the number of withdrawals.

### Sample size calculation

The sample size was determined by a power calculation based on resting LVEF outcome, using a non-commercial statistical power analysis program (G*Power Version 3.1.9.2). Based on an effect size of 0.6 for resting LVEF presented in a previous study [26], to ensure statistical power of 80% and a significance level of 0.05, using the *t* test for two independent groups, the recruitment of 72 participants is required. Predicting a 20% dropout rate [19], we estimate that a total of 90 patients will be needed (45 in each arm). There are no planned early stopping rules. Adverse events will be evaluated by the study investigators, who will make the decision to stop the study early if there is a clinically relevant increased risk.

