## Background

Over the last three decades the epidemiology of breast cancer (BC) has been marked by the clear increase in survival rates [1]. The accessibility of screening and the discovery of new therapeutic options are among some relevant factors related to the improved management of cancer. However, despite their undeniable clinical importance, anti-cancer treatments are also associated with frequent induction of side effects. Among those, cardiotoxicity emerges as a major challenge, limiting treatment options [2] and contributing to morbidity and mortality in this patient population [3–5].

In the BC setting, cardiotoxicity is typically associated with exposure to traditional cytotoxic therapies and particularly with the use of anthracyclines [6]. Anthracyclines are important and effective chemotherapeutic agents, frequently administered in curative and palliative regimens for BC, although their clinical use is limited by cardiac dysfunction, usually seen as cardiotoxicity [7]. The American Society of Echocardiography and European Association of Cardiovascular Imaging define cardiotoxicity as a decrease in left ventricular ejection fraction (LVEF) of > 10% to a value of < 53% [8]. However, it has been proposed that anthracycline-related cardiotoxicity (ARC) is a continuous [9] and dose-dependent phenomenon [10] that starts with acute myocardial damage [11], which can be detected by elevation of circulating cardiac biomarkers [12] and by impairment of left ventricular (LV) longitudinal strain [13], in turn preceding the commonly reported progressive decline in LVEF [9]. ARC may ultimately lead to overt heart failure, particularly when underestimated, not prevented or insufficiently prevented, or untreated, [9].

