Currently, exercise is recognized as a safe and effective, supportive intervention to improve physical function and HR-QOL in BC survivors during [19] or after treatment [20]. Furthermore, exercise has also been proposed as a potential tool to mitigate ARC in humans [21, 37], although this remains uncertain as it is mainly supported by data from animal studies and/or using less accurate biomarkers [22, 23]. In fact, there are limited data on whether the benefits of exercise also include protection from anthracycline-related cardiac damage in women with BC. To the best of our knowledge, Kirkham et al. [24] were the first to test this hypothesis by analyzing the efficacy of a single aerobic bout performed 24 h prior to each treatment. The authors observed positive effects on systemic outcomes (cardiac output, resting HR, body weight, and psychological symptoms), but did not observe relevant changes in echocardiographic outcomes (LV mass, LV ejection fraction, strain imaging, and the E/A ratio) or circulating cardiac biomarkers (troponin t and NT-proBNP). In a recent non-randomized trial, Howden et al. [26] verified that performing a 2-weekly supervised exercise program plus a weekly unsupervised aerobic session attenuated the reduction in peak Vo_2_ and the increase of troponin levels in women with BC undergoing AC-CT, when compared to a usual care group. However, these authors did not observe any relevant changes in the measured echocardiographic outcomes. So far, the overall clinical significance of exercise in preventing cardiac dysfunction associated with anthracycline treatment remains to be clarified in controlled clinical settings.

The present study will explore the cardioprotective role of exercise and potential mitigation of ARC, and establish the possible effect of exercise on different health outcomes in women with BC. A total of 90 adult women with early BC and prescribed AC-CT at the CHVNG/E will be enrolled. Recruitment will take place between 1 November 2018 and 31 November 2020 (expected date of recruitment completion). Follow up is expected to be completed by 30 June 2021.

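### The LVEF effect of 0.6 that sizes the trial is not reconciled with the article's own account of its source, and 72 evaluable patients give the stated 80% power only with a one-sided test

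*Protocol article*

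**What the plan says.** The Sample size calculation section of the protocol article uses resting LVEF alone, one of three primary outcomes, to size the trial. The input is a standardised effect: "Based on an effect size of 0.6 for resting LVEF presented in a previous study [26". The target is given as "to ensure statistical power of 80% and a significance level of 0.05", with a t "test for two independent groups", and the result is that "the recruitment of 72 participants is required". Allowing for 20% dropout brings the total to 90, or 45 per arm. The section does not say whether the test is one- or two-sided. It gives no LVEF difference in points, SD, interval or time point, and does not say whether 0.6 is a difference between arms or a change within one.

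The Discussion introduces reference 26 with "In a recent non-randomized trial", credits it with benefits on peak oxygen consumption and troponin, and adds that "these authors did not observe any relevant changes in the measured echocardiographic outcomes". The section on assessment of the primary outcomes makes clear that LVEF is an echocardiographic measure in this trial.

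The Statistical analyses section plans a between-arm ANCOVA adjusted for the baseline value, with significance at p below 0.05, again without stating sidedness.

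**The concern.** One source is used in two ways that do not sit together: as the origin of a medium-to-large LVEF effect, and as a study that saw nothing relevant on echocardiography. No other justification for 0.6 is offered, so the stated power depends wholly on a figure whose derivation the reader cannot follow.

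The stated power also has a problem that does not depend on the source. Even if 0.6 is accepted, 72 evaluable patients do not give 80% power under the usual two-sided reading of a 0.05 significance level. A reader who takes 80% at face value will overestimate what the trial can detect on LVEF.

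**Working it through.** **Inputs.** Effect d = 0.6, power 80%, alpha 0.05, two-group t test, 72 evaluable and 20% dropout, all from the Sample size calculation section. The 1:1 allocation in the Randomization section gives n = 36 per arm.

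**Method.** Under a true effect d, the t statistic with n per arm follows a noncentral t distribution with 2n − 2 degrees of freedom and noncentrality d × √(n/2). Power is the probability of passing the critical value.

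**1. Reproducing the plan's figure.**
- One-sided alpha 0.05: the required n is 35.04 per arm, rounded up to 36, so 72 in total. This matches.
- Two-sided alpha 0.05: the required n is 44.59 per arm, rounded up to 45, so 90 in total. This does not match.
- Dropout: 72 / (1 − 0.20) = 90. This matches.

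The stated figure is therefore a one-sided calculation, although the section does not say so.

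**2. Power with 36 per arm at d = 0.6.** Noncentrality is 0.6 × √18 = 2.55 on 70 degrees of freedom.
- One-sided: 81%.
- Two-sided: 71%.

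Two-sided power of 80% at 0.6 needs 90 evaluable patients, which is 90 / 0.80 = 112.5, or 113 recruited after 20% dropout. With 72 evaluable, the effect detectable with 80% two-sided power is 0.67.

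**3. Power with 36 per arm if the true effect is smaller.** The documents give no alternative value, so these are assumed effects shown as a range.

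| Assumed d | One-sided 0.05 | Two-sided 0.05 |
|---|---|---|
| 0.6 | 81% | 71% |
| 0.5 | 68% | 55% |
| 0.4 | 51% | 39% |
| 0.3 | 35% | 24% |

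**4. Allowing for the planned ANCOVA.** Adjusting for a baseline value with correlation ρ to follow-up divides the residual SD by its gain, so the effective effect is d / √(1 − ρ²). The article gives no ρ. With ρ assumed to be 0.5, the divisor is √0.75 = 0.866:
- d = 0.6 becomes 0.69, two-sided power 83%.
- d = 0.4 becomes 0.46, two-sided power 49%.
- d = 0.3 becomes 0.35, two-sided power 31%.

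With ρ assumed to be 0.3, two-sided power at 0.6 is 75%; with 0.7 it is 94%.

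**5. Can both statements about reference 26 be true?** An observed d is significant at two-sided 0.05 only if it exceeds t(0.975; 2m − 2) × √(2/m), with m per arm. At m = 22 this threshold is 0.608, and at m = 25 it is 0.569. So with about 22 or fewer per arm, an observed 0.6 would not be significant. At 22 per arm its approximate 95% interval runs from 0.00 to 1.20. The size of reference 26 is not in the article, so this only shows what is possible.

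**The case against.** The strongest defence is that the two statements need not conflict. A small study can show a point estimate of 0.6 that is not significant, and its authors can fairly report no relevant change (step 5). This stands. A reader might infer that 0.6 is absent from reference 26, or that the citation should be withdrawn, but the article cannot show either. What remains is that an estimate of that kind would be imprecise, and the article does not explain it.

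A second defence is that 71% at an effect of 0.6 has nothing to do with the source. That is right. The drop from 81% to 71% comes from sidedness alone; only the fall down the rows of the table reflects doubt about 0.6.

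A third is that the planned analysis is a baseline-adjusted ANCOVA, so an unadjusted t test understates power. This also stands: an assumed correlation of 0.5 brings two-sided power at 0.6 above 80%. It does not restore power at 0.3 or 0.4. The gain also presumes that 0.6 was standardised by the SD of the follow-up value, which the article does not say.

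Three further inferences are tempting but not supported. The Background places biomarker and strain changes early, "in turn preceding the commonly reported progressive decline in LVEF", but it gives no standardised between-arm effects, so it does not establish that LVEF is the primary outcome least likely to show 0.6. The other human study described in the Discussion reported benefits elsewhere "but did not observe relevant changes in echocardiographic outcomes", but it tested a single aerobic bout before each treatment, not a thrice-weekly programme. And nothing in the article says that a null LVEF result will be presented as evidence of no effect.

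**Conclusion.** The point holds in two limited parts. First, the sample-size section and the Discussion describe reference 26 in ways that are not reconciled, so the derivation of the only planning effect is unclear. This does not prove 0.6 wrong. Second, the stated 80% power with 72 evaluable patients is correct only for a one-sided 0.05 test (81%). The two-sided t test gives 71%, and 80% needs about 90 evaluable.

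The power figures assume equal arms, 36 evaluable per arm and an unadjusted t test. How far power falls short on account of the planning effect cannot be fixed from the document, because the true effect is unknown; the range in the table is the most that can be said. The ANCOVA figures rest on assumed baseline correlations.

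**What to change.** 1. Reconcile the Sample size calculation section with the Discussion. State which contrast, time point and SD produced 0.6 from reference 26, or present 0.6 as a planning assumption.
2. State the sidedness and restate power at 72 evaluable for effects from 0.3 to 0.6, using the table above. Add that the baseline-adjusted ANCOVA would raise these values, and give the baseline correlation assumed.
3. Report the LVEF result as the baseline-adjusted difference between arms with its 95% CI.

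The cost is text only. No extra patients are needed and the planned analysis does not change. The downside is that the power on record becomes less favourable than 80% if the two-sided t test is used.
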